### A comprehensive quality assessment toolkit for aphasia care after stroke: the MEASuRES minimum dataset

The MEASuRES (Meaningful Evaluation of Aphasia SeRvicES) minimum dataset was developed in partnership with researchers, clinicians and people with aphasia and their families, to address the gap in routine aphasia-specific data collection and reporting. MEASuRES (box 1) comprises four elements (sociodemographic characteristics, quality indicators, treatment descriptors, outcome measurement instruments) and builds on three international multistakeholder initiatives to standardise aphasia data and outcome collection and description: the DESCRIBE reporting standards project (DESCRIBE^28^), the Research Outcome Measurement in Aphasia COS (ROMA COS^29^) and the International Population Registry for AphasIa after StrokE (I-PRAISE^30^).

Box 1Data items included in the measures minimum datasetSociodemographic characteristics^28^
Person with aphasia.Age.Biological sex.Years of education.Language of assessment and treatment.Primary language spoken at home.Languages used.History of condition known to impact communication or cognition.History of previous stroke.Lesion hemisphere.Time since onset of aphasia.Conditions arising from the neurological event.Communication partner.Age.Biological sex.Relationship to person with aphasia.Quality indicators^36^
A screener and/or assessment is completed to determine if communication impairment (including aphasia) is present.A valid and reliable standardised assessment is conducted to determine aphasia severity.Information about aphasia is provided to the person with aphasia.Information about aphasia is provided to the person with aphasia’s primary carer/communication partner.Information about support is provided to the person with aphasia’s primary carer/communication partner.The primary carer/communication partner of the person with aphasia is provided with communication partner training.Individualised recommendations for communicating with the person with aphasia are provided to the treating team.There is training for staff in supported communication for aphasia.Goal setting is undertaken in partnership with the person with aphasia and their significant others.The person with aphasia receives person-centred/family-centred care.The person with aphasia receives speech and language therapy.Treatment descriptors^30^

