### Study design and setting

This multicentre observational pilot study will be conducted in a convenience sample of five Australian publicly funded, metropolitan, tertiary health services providing stroke care: Metro North Hospital and Health Service (Queensland), St Vincent’s Hospital Melbourne (Victoria), Monash Health (Victoria), Sir Charles Gairdner Osborne Park Health Care Group (Western Australia) and Fiona Stanley and Fremantle Hospital Group (Western Australia).

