### Planned analyses

Data quality and completeness will be summarised using descriptive statistics. For each variable in the minimum dataset, the proportion completed will be calculated to determine patterns of missing, incomplete or invalid data. Missing data will be handled in accordance with the processes outlined in existing guidelines.^53 54^

Similarly, descriptive statistics will be used to summarise patient characteristics, adherence to quality indicators, treatment descriptors and scores on aphasia outcome measurement instruments. Adherence to quality indicators will be defined as the proportion of eligible episodes of stroke in which the indicator was provided, estimated overall and at the hospital level. We will also summarise the total number of indicators provided per episode at each hospital. Associations between patient characteristics, adherence to quality indicators and aphasia outcomes will be determined using multilevel regression models, adjusted for clustering effect within the hospital. The type of regression models to be used for analysis will depend on the nature and distribution of the outcome variables. All regression models will also be adjusted for covariates, including age and baseline scores on the aphasia outcomes and other covariates based on data collected.^53^

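### The per-episode indicator total has no denominator of applicable indicators, so hospital totals can differ through communication-partner availability alone

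*Protocol article*

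**What the plan says.** Under Study 1, Planned analyses, the protocol article sets out two summaries of the quality indicators in consecutive sentences. The first has an eligibility denominator: "Adherence to quality indicators will be defined as the proportion of eligible episodes of stroke in which the indicator was provided", estimated overall and by hospital. The second does not: "We will also summarise the total number of indicators provided per episode at each hospital".

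The indicators are listed in Box 1. Three are directed at the partner rather than the patient:
- "Information about aphasia is provided to the person with aphasia’s primary carer/communication partner"
- "Information about support is provided to the person with aphasia’s primary carer/communication partner"
- "The primary carer/communication partner of the person with aphasia is provided with communication partner training"

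One describes the service: "There is training for staff in supported communication for aphasia".

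The four eligibility criteria (Study 1, Participants and sample size) do not ask for a communication partner. The setting is a "convenience sample of five Australian publicly funded, metropolitan, tertiary health services".

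**The concern.** The first sentence accepts that not every episode is eligible for every indicator. The second drops that distinction. Read literally, a carer item that could not be delivered because there was no carer adds nothing to the total, exactly as if it had been omitted. The total then mixes two things: how much applicable care was given, and how many patients had a partner to whom part of it could be given.

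This matters because the article expects site-specific information on evidence-practice gaps to feed later quality improvement (Anticipated outcomes), and sites will receive a summary of findings (Dissemination plan). A hospital with fewer partnered patients could appear to deliver less care when it delivers the same.

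Staff training raises a separate and smaller point. It is a feature of the service, so it does not belong in a count of what was provided in an episode.

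**Working it through.** The article states no figure for the total, so there is nothing to reproduce. The check is a count followed by an expected value.

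**Inputs from the article**
- Indicators in Box 1, by counting: 11.
- Directed at the carer or partner: 3 (aphasia information, support information, partner training).
- Describing the service: 1 (staff training).
- Remaining patient-level indicators: 11 − 3 − 1 = 7.

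**Inputs assumed, because the article gives none**
- a: the proportion of applicable patient-level indicators delivered, the same at all hospitals.
- s: the share of a hospital's episodes with a partner.
- t: 1 if the hospital has staff training, 0 if not.

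**Attainable maximum**
- With a partner: 7 + 3 + 1 = 11.
- Without: 7 + 0 + 1 = 8.

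**Expected raw total per episode** = 7a + 3as + t. With a = 0.80 and t = 1 at both hospitals:
- s = 0.90: 5.60 + 2.16 + 1 = 8.76.
- s = 0.60: 5.60 + 1.44 + 1 = 8.04.
- Gap: 0.72 indicators, with no difference in care.

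**General gap** = 3 × a × (s1 − s2). The term t cancels when training is the same at both hospitals.

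| a | s1 v s2 | Gap |
|---|---|---|
| any | equal | 0.00 |
| 0.6 | 0.90 v 0.80 | 0.18 |
| 0.8 | 0.90 v 0.70 | 0.48 |
| 0.8 | 0.90 v 0.60 | 0.72 |
| 1.0 | 1.00 v 0.50 | 1.50 |

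The count of three may be low. One further item reads "Goal setting is undertaken in partnership with the person with aphasia and their significant others". If it were scored as not provided when there is no partner, the 0.72 would become 4 × 0.8 × 0.3 = 0.96.

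**Scale.** At a = s = 0.8, with indicators delivered independently (an assumption), the variance of the total has two parts:
- Seven core items: 7 × 0.8 × 0.2 = 1.12.
- Carer items: 0.8 × (3 × 0.16 + 2.4²) − (0.8 × 2.4)² = 1.31.

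The SD is √2.43 ≈ 1.56. With 40 episodes per service (200 / 5, an equal split being assumed), the standard error of a mean is about 0.25. A gap of 0.72 would be visible against that.

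**With the applicable denominator.** Patient-level indicators provided over applicable = (7a + 3as)/(7 + 3s) = a. At a = 0.80 this gives 0.80 at both hospitals, whatever s is.

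That cancellation is exact only if carer items and other items are delivered equally often. Suppose carer items are delivered at 0.6 and the other seven at 0.8. The mean per-episode ratio is 0.8 − 0.3 × s × (0.8 − 0.6), which is 0.746 at s = 0.90 and 0.764 at s = 0.60. The residual gap is 0.018. The raw count would differ by 3 × 0.6 × 0.3 = 0.54 of 10 patient-level items, or 0.054 on the same scale. The ratio reduces the artefact without always removing it.

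**The case against.** The strongest defence is that the main measure already handles eligibility. An episode without a partner can be left out of the denominator for each carer item under the stated definition, so the single-indicator proportions are sound. The count is introduced as an additional descriptive summary in an observational pilot. Partner characteristics are collected and could be shown beside it. A fuller analysis plan, not available here, may define applicability. All of this stands and limits the weight of the point. It does not remove it: the article states a count without a denominator directly after a rule that has one, and a reader following the text would compute the raw count.

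Three stronger readings are tempting and are not supported.

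- **Hospitals giving identical care will show different totals.** They will only if partner shares differ. The article allows proxy consent in Queensland and Victoria but not in Western Australia. That makes a difference in partner share plausible, but a proxy is not necessarily a communication partner and no share is given. Nor does staff training create such a gap, because identical care includes identical training.
- **Hospitals would be ranked on case mix.** The text says the total will be summarised. It plans no ranking, test or benchmark on the total, and no model is stated to use it.
- **Testing staff training against outcomes would inflate false positives.** The article plans associations between indicator adherence and outcomes but leaves the model type open. It does not say that this indicator is tested on its own or which test is used, and it counts health services rather than hospitals. Any error rate would rest on an analysis the article does not state.

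**Conclusion.** The point holds in a limited form. As worded, the per-episode total has a ceiling of 11 for some episodes and 8 for others, so hospital totals can differ through partner availability alone. The illustrative size is 0.72 indicators at 80% adherence with partner shares of 90% and 60%. The range is 0.18 to 1.50 over the assumptions shown, and zero if shares are equal. The counts of 11, 3 and 1 come from Box 1; the adherence levels and partner shares are assumptions. The consequence is confined to a secondary descriptive summary. It is worth correcting because the change is small and the summary may inform feedback to sites. The staff-training item is a matter of unit: it describes a service and should not be scored per episode.

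**What to change.** Replace the sentence on the total with a rule of this kind: for each episode, report the number of patient-level indicators provided divided by the number applicable to that episode, and summarise this by hospital. The three carer items are not applicable when no communication partner is recorded. State whether goal setting is applicable without a significant other. The raw count can be shown alongside. Report staff training once per service, outside the episode-level score.

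Two details make the rule work. The database should separate an episode with no partner from one with missing partner data, otherwise a blank field would wrongly shrink the denominator. The single-indicator proportions should be kept beside the ratio, because the ratio can still shift slightly with partner share when carer items are delivered less or more often than the rest.

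The cost is one derived variable and a sentence of wording. Box 1 already includes the partner's age, sex and relationship to the patient. The small downside is that a ratio is slightly less simple to read than a count.

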### Study 2: process evaluation of piloting the MEASuRES minimum dataset

This process evaluation will evaluate the performance of the MEASuRES minimum dataset, and to explore its acceptability and feasibility in clinical settings, from the perspective of patients and speech pathologists.

### Study design and setting

This mixed-methods process evaluation^55^ will involve (a) patient and clinician surveys completed during administration of the minimum dataset (study 1); (b) semistructured interviews conducted with speech pathology clinicians following completion of the pilot study (study 1) and (c) integration of REDCap and site-specific training and implementation data.

### Recruitment and consent

The process evaluation will involve two participant groups: people with aphasia and speech pathologists. All people with aphasia (or their proxy) who consented to participate in study 1 (maximum n=200) will be invited to complete a survey prior to discharge from hospital to explore their experiences of completing the minimum dataset. When consenting for study 1, participants will be provided with written, aphasia-friendly participant information and consent forms describing the research activities associated with study 2. Speech pathologists will provide communication support throughout the consenting process. The survey will be in an aphasia-friendly format and administered in-person by speech pathology clinicians with provision of communication support.

All speech pathologists who administer the minimum dataset data in study 1 (n= ~25) will be invited to complete two online surveys throughout (time point 1) and at the completion (time point 2) of study 1, to explore the performance of the minimum dataset, and their perspectives of administering the minimum dataset in clinical settings. In addition, expressions of interest will be sought from speech pathologists to participate in semistructured interviews at the completion of study 1. Of those who express interest, 15 clinicians who meet the following eligibility criteria will be invited to participate in the interviews: (1) being a qualified speech pathologist, (2) being employed by a participating health service and (3) having participated in the pilot administration of the MEASuRES minimum dataset (study 1). Purposive sampling of clinicians across years of experience, clinical setting and health service sites will be applied to ensure a range of viewpoints. These interviews will serve to contextualise survey results and provide further insights from the participating clinicians. Additional interviews will be conducted where required. Consent will occur in-person or online, following the opportunity to discuss participation with the research team. The consent process will be conducted by a staff member of the research team.

### Data collection

Survey elements will be designed in alignment with previous surveys used to evaluate COS and minimum dataset implementation.^56^ Semistructured interview questions will be based on previous research investigating barriers and facilitators to COS use and aphasia treatment delivery,^57^ and will consider all aspects of piloting the minimum dataset (ie, including collection of demographic data and quality indicators). Acceptability and feasibility will be explored through survey and semistructured interview data. A log of site-training and factors influencing implementation of the minimum dataset will be maintained, along with routinely collected administrative data.

### Planned analyses

Descriptive statistics will be used to summarise quantitative data from the surveys and interviews.^53^ Qualitative survey and interview data will be analysed using content analysis,^58^ to explore the performance of the minimum dataset and to understand the experiences of people with aphasia and speech pathology clinicians. The qualitative data will be compared and integrated with quantitative findings using a convergent interactive design.^59^ Barriers and facilitators to administering the dataset will be mapped to the theoretical domains framework^60^ and behaviour change wheel^61^ to support future scaling.

Findings from the different data sources (surveys, interviews, REDCap, training and implementation logs) will be integrated and compared using the Medical Research Council process evaluation framework^55^ to understand the relationships between implementation, contextual factors and other mechanisms of impact.

### Development of the analysis tool

The analysis tool is designed to provide objective interpretation of meaningful changes following aphasia treatment. In study 3, we will determine thresholds of meaningful change on patient-reported anchor scales (figure 2). These anchor scales were adapted from the anchor question proposed by Revicki *et al* to be conceptually relevant to core outcomes in aphasia (ie, language, communication, quality of life and emotional well-being^62^). As a patient-rated measure, labels for the indicators on the anchor scale were selected based on ease of understanding by patients with aphasia. While an indicator for +3 (completely recovered) represents a potential perceived outcome for participants early after stroke onset, an acceptable indicator for −3 (a point lower than −2=much worse) could not be identified. As such, the anchor scale was developed with six response categories including a neutral response option, in line with existing research.^63^ In study 4, the agreed thresholds on the anchor scale (study 3) will be applied to treatment outcome data (study 1), establishing MIC values for the ROMA COS.

**Figure 2 F2:**
[figure not shown]
Example of a patient-reported 6-point Likert anchor scale, adapted from previous research.^62^

### Study 3: establishing consensus-based thresholds for the calculation of MIC values

The aims of study 3 are to determine thresholds of meaningful change from the perspectives of people with aphasia and speech pathologists. Stakeholder perspectives have seldom been included in determining the threshold of clinically meaningful change on anchor rating scales.^64^ By undertaking a stakeholder-focused approach, the resulting MIC values will be clinically meaningful and relevant to the experiences of people with aphasia.^65 66^ Outcomes from this study will inform the anchor-based predictive modelling methodology for establishing MIC values (see study 4).

### Setting and design

People with aphasia and speech pathologists will participate in online focus groups and a consensus meeting to discuss clinically important change in aphasia, and to establish the threshold for a meaningful change based on the anchor scales (figure 2).

### Participants and sample size

An expert panel of people with poststroke aphasia (n=10) and speech pathologists (n=10) will be convened. Exclusion criteria for people with aphasia include: (a) aetiology other than stroke, (b) neurological, cognitive or sensory condition that impedes ability to participate and (c) being unable to verbally or non-verbally communicate a yes/no response. Exclusion criteria for speech pathologists: does not work in poststroke aphasia rehabilitation. People with aphasia will be purposively sampled for: sex (male, female), time poststroke (1 week to 6 months, >6 months); age (<65 years, ≥65 years of age) and severity of aphasia (mild, moderate, severe aphasia per the Aphasia Severity Rating Scale^67^). Speech pathologists will be purposively sampled for work setting (inpatient rehabilitation, community rehabilitation). Participants will be consented to the study in alignment with the sampling criteria. It is anticipated that 10 people with poststroke aphasia and 10 speech pathologists will be sufficient to inform a threshold for meaningful change. Each participant will attend one focus group. A maximum of five participants will attend each per group. The final number of focus groups will be determined in part by the amount of time and level of communication assistance each participant will require to understand and meaningfully participate, and in part by the analysis of focus group findings. All participants will attend the consensus workshop.

### Recruitment and consent

Expressions of interest will be sought from people with aphasia, via local and national stroke and aphasia research centres and consumer organisations including their social media channels. All prospective participants will be provided with communicatively accessible information about the study. A meeting will be held to answer questions and obtain demographic details for sampling. Participants who respond correctly to yes/no questions about the study’s purpose and participation requirements will be invited to consent. Project investigators who are speech pathologists will provide communication support throughout the consenting process.

To reduce the burden of participation, honorarium payments will be offered for time spent participating in study 3. Participants with aphasia will be remunerated at a rate of $A40 per hour, for an estimated total of five hours per participant (consent meeting, focus group, consensus workshop), in accordance with recommendations from Health Consumers Queensland.^49^ Speech Pathologists will be reimbursed at a rate of $A60 per hour for an estimated total of four hours per participant (focus group, consensus workshop), commensurate with the Queensland Health HP4 casual hourly rate.

### Data collection and planned analyses

Focus groups and the consensus workshop will be recorded and transcribed. Data will be analysed using content analysis.^58^ In the consensus workshop, participants will vote on whether different thresholds of meaningful change should be established for participant subgroups (eg, aphasia severity or time post-onset). Participants will vote on the threshold for important change on anchor scales for each construct (ie, language, communication, emotional well-being, quality of life) as these may differ. Quantitative data will be analysed using descriptive statistics (percentages of responses). Consensus will be defined a priori as≥70% agreement.

### Study 4: establishing MIC values for the ROMA COS

This study will involve integrating and analysing data from studies 1 and 3 to establish MIC values for the ROMA COS.^44^

### Design

Anchor-based predictive modelling approach to establishing MIC.

### Data collection

As part of study 1, the ROMA COS will be administered prior to and after usual care aphasia intervention, with a minimum interval of 2 weeks. When consenting for study 1, participants will be provided with written, aphasia-friendly participant information and consent forms describing the research activities associated with study 4. Speech pathologists will provide communication support throughout the consenting process. With the second administration of the ROMA COS, both participant groups (people with aphasia and clinicians) will additionally rate perceived change in language, communication, quality of life and emotional well-being on corresponding anchor scales (figure 2). The second ROMA COS and anchor scales will be collected prior to discharge from inpatient care at the participating health service site. In instances where this is not feasible, outpatient follow-up will be undertaken, following a flexible approach to delivery mode and assessor in line with site-specific agreements.

